# Cognitively-Based Compassion Training versus cancer health education to improve health-related quality of life in survivors of solid tumor cancers and their informal caregivers: study protocol for a randomized controlled pilot trial

**DOI:** 10.1186/s13063-019-3320-9

**Published:** 2019-04-29

**Keywords:** Cancer survivorship, Health-related quality of life, Compassion meditation, Dyadic interdependence, Inflammation, Cortisol, Active control

## Abstract

**Background:**

Cancer survivors and their informal caregivers (family members, close friends) often experience significant impairments in health-related quality of life (HRQOL), including disruptions in psychological, physical, social, and spiritual well-being both during and after primary cancer treatment. The purpose of this in-progress pilot trial is to determine acceptability and preliminary efficacy (as reflected by effect sizes) of CBCT® (Cognitively-Based Compassion Training) compared with a cancer health education (CHE) attention control to improve the primary outcome of depressive symptoms and secondary outcomes of other HRQOL domains (e.g., anxiety, fatigue), biomarkers of inflammation and diurnal cortisol rhythm, and healthcare utilization-related outcomes in both cancer survivors and informal caregivers.

**Methods:**

Forty dyads consisting of solid tumor survivors who have completed primary treatments (chemotherapy, radiation, surgery) and their informal caregivers, with at least one dyad member with ≥ mild depressive symptoms or anxiety, will be recruited from Tucson, Arizona, USA. Survivor-caregiver dyads will be randomized together to complete either CBCT or CHE. CBCT is a manualized, 8-week, group meditation-based intervention that starts with attention and mindfulness and builds to contemplative practices aimed at cultivating compassion to the self and others. The goal of CBCT is to challenge unexamined assumptions about feelings and behaviors, with a focus on generating spontaneous self-compassion and increased empathic responsiveness and compassion for others. CHE is an 8-week, manualized group intervention that provides cancer-specific education on various topics (e.g., cancer advocacy, survivorship wellness). Patient-reported HRQOL outcomes will be assessed before, immediately after (week 9), and 1 month after CBCT or CHE (week 13). At the same time points, stress-related biomarkers of inflammation (e.g., plasma interleukin-6) and saliva cortisol relevant for survivor and informal caregiver wellness and healthcare utilization will be measured.

**Discussion:**

If CBCT shows acceptability, a larger trial will be warranted and appropriately powered to formally test the efficacy of this dyadic intervention. Interventions such as CBCT directed toward both survivors and caregivers may eventually fill a gap in supportive oncology care programs to improve HRQOL and healthcare utilization in both dyad members.

**Trial registration:**

Clinicaltrials.gov, NCT03459781. Prospectively registered on 9 March 2018.

**Electronic supplementary material:**

The online version of this article (10.1186/s13063-019-3320-9) contains supplementary material, which is available to authorized users.

## Background

Advancements in early detection and treatments have dramatically improved prognosis for the majority of patients diagnosed with solid tumor cancers. Recent trend data show that 5-year survival rates are improving for those treated for colorectal (66%), prostate (99%), and breast cancer (women, 90%) [1]. Despite these gains, health-related quality of life (HRQOL) impairments remain significant for cancer survivors both during and after treatment. For example, after diagnosis and the end of primary treatment, survivors of colorectal, prostate, and breast cancer are likely to experience elevated depressive symptoms (i.e., 28% [2], 18% [3], and 10–25% [4, 5], respectively), fatigue (23–73% [2, 6], 12–21% [7], and 30–80% [8–10], respectively), and anxiety symptoms (including fear of recurrence) [11–16].

While the focus on HRQOL in cancer survivorship is often on cancer survivors themselves, informal caregivers (hereafter referred to as caregivers; i.e., family members and friends who provide supportive care for cancer survivors) also suffer HRQOL impairments. A sizable portion of these caregivers experience increased depressive symptoms and distress, not just around the time of diagnosis and during primary treatments, but also after primary cancer treatments have ended for the cancer survivor [17–19]. Impairments experienced by caregivers are significant for several reasons. Caregivers provide significant supportive care (as much as 60%) to their loved one diagnosed with and treated for cancer [19–21], and HRQOL impairments can undermine their effectiveness in this role. Quality of life of caregivers is important and significant in its own right, and stress experienced by caregivers may have an impact on stress-responsive physiology, including cortisol and inflammation. These stress biological changes may accompany an increased risk for chronic medical and psychiatric illness experienced by caregivers [22–24].

Although there are many interventions to improve HRQOL for cancer survivors, there are few for caregivers, and still fewer that engage both survivors and caregivers together. The dearth of programs that engage survivors and caregivers together is a significant gap. Work by our group has shown that increased depressive symptoms, anxiety, symptom distress (including fatigue), and positive affect that breast (or prostate) cancer survivors experience are interdependent with the same impairments that their caregivers experience, and vice-versa [25, 26]. Caregivers are therefore much more than a “social backdrop” to cancer and its treatment [25]. Instead, HRQOL is shared by both members of a cancer survivor dyad, perhaps by way of “emotional contagion,” or through the multilevel phenomenon whereby stimuli from one individual results in a complimentary emotional or behavioral state in another individual (i.e., the “common fate” model) [27]. We believe that our findings suggest that interventions to promote HRQOL in either cancer survivors or their caregivers should be directed at both members of the dyad simultaneously to leverage emotional contagion to promote the sharing of positive affect, potentially dismantling the possibility of shared negative affect.

CBCT® (Cognitively-Based Compassion Training) is a manualized 8-week, meditation-based intervention that cultivates empathy and prosocial capacity and enhances perceptions of social connection and positive emotions for others [28]. CBCT is “cognitively-based” in that it relies on an analytical method of meditation to gain deeper understanding of a particular topic [29]. The intervention begins by teaching mindfulness practices and builds on this heightened awareness to facilitate constructive emotional states, self-compassion, and feelings of social connectivity [28]. We have found that CBCT improves a number of different HRQOL dimensions in breast cancer survivors, including symptoms of depression, fear of cancer recurrence, and vitality [30]. We have also found that CBCT has other health-related benefits in nonsurvivors, including reduced stress-related inflammation in young adults and foster care adolescents [30–36]. These findings suggest that CBCT is likely to be feasible for use in survivors of other solid tumor cancers and may promote positive changes in key aspects of HRQOL in the same individuals. However, CBCT has not been tested before with survivors other than those of breast cancer who have different treatments and prognoses, or with caregivers of solid tumor cancer survivors. Therefore, in the present pilot trial we will investigate acceptability of CBCT, as well as an active attention control condition called cancer health education (CHE) for both solid tumor cancer survivors and their caregivers.

Besides acceptability of CBCT and CHE, we will also evaluate effect sizes for the differences between CBCT and CHE on several outcomes especially relevant for survivors and caregivers. The primary outcome among these will be depressive symptoms, a key domain of psychological HRQOL. Secondary outcomes will include other HRQOL domains (anxiety, positive affect, fatigue, empathy, feelings of social connection), global HRQOL, dyadic function, and self-compassion. We will also assess stress-related biomarkers and healthcare utilization as secondary outcomes. Considerable evidence, including work by our group, suggests that HRQOL impairments in cancer survivors are causally linked to changes in stress-related physiological function, including diurnal cortisol production and biomarkers of inflammation (plasma interleukin (IL)-1β, IL-6, and tumor necrosis factor (TNF)-α; peripheral blood mononuclear cell (PBMC) nuclear factor-κB (NF-κB)) [37, 38]. HRQOL impairments (e.g., depression) have also been found to be associated with poor use of healthcare resources in cancer survivors [39]. The current trial will begin to extend our earlier findings with breast cancer survivors to survivors of other cancers, and CBCT will be conducted for the first time in a form where both cancer survivors and their caregivers take part in CBCT together. If CBCT and CHE are acceptable to survivors and caregivers, a larger trial in the future will be justified. To avoid the possibility of a floor effect with the outcomes assessed (especially psychological HRQOL; i.e., depression and anxiety), and because prior research with CBCT suggests brain systems implicated in compassion may show beneficial change when depression symptoms improve while learning CBCT [34], the study will enroll dyads with a survivor and/or caregiver with ≥ mild depressive and/or anxiety symptoms (according to PROMIS distress-depression or distress-anxiety four-item scales).

The overarching prediction of the current pilot trial is that participation in CBCT or CHE will be acceptable to solid tumor cancer survivors and their caregivers. We will also capture effect sizes for outcomes noted above for the comparisons of participants randomized to either CBCT or CHE. The following aims guide the pilot trial.

### Study aims and hypotheses

Aim 1 is to demonstrate acceptability of CBCT and CHE for solid tumor cancer survivors and their caregivers. We predict that both CBCT and CHE will be acceptable for use with survivor-caregiver dyads, as reflected by > 75% average attendance at weekly CBCT classes, and > 75% average attendance at weekly CHE classes.

Aim 2 is to estimate effect sizes for the differences between CBCT and CHE at weeks 9 and 13 on HRQOL-related outcomes including outcomes of psychological HRQOL (depressive symptoms (primary outcome), anxiety, positive affect, and self-compassion), physical HRQOL (fatigue), and social HRQOL (empathy, feelings of social connection/isolation, dyadic function) as well as global well-being. Differences between groups at weeks 9 and 13 on HRQOL-related outcomes will be used to inform sample size calculations for a full-scale clinical trial.

Aim 3 is to estimate effect sizes between groups at weeks 9 and 13 on stress-related biomarkers of inflammation (plasma IL-6, IL-1β, TNF-α, NF-κB pathway activation), as well as diurnal saliva cortisol rhythm in survivor-caregiver dyads randomized to CBCT compared with survivor-caregiver dyads randomized to CHE. Differences between groups at weeks 9 and 13 on biomarker outcomes will be used to inform sample size calculations for a full-scale clinical trial.

Aim 4 is to estimate effect sizes for the differences between CBCT and CHE at weeks 9 and 13 on healthcare utilization (i.e., keeping appointments, use of preventive services, hospitalizations, and use of urgent care or emergency department services), and patient activation (i.e., motivation, knowledge, skills and confidence in managing personal health). Differences between groups at weeks 9 and 13 on healthcare utilization outcomes will be used to inform sample size calculations for a full-scale clinical trial.

## Methods

### Study design, allocation procedures, and blinding

This interventional study uses a randomized controlled trial design to compare CBCT with CHE to determine effect sizes in study outcomes (see below). Participants review and sign the informed consent form in the presence of either the Principal Investigator or a study coordinator after a script is read aloud to them that describes the study. Enrolled dyads are randomized 1:1 in blocks of two dyads to either CBCT (*n* = 20 dyads) or the attention control (*n* = 20 dyads). CBCT and CHE groups are run concurrently. Group assignment to either CBCT or CHE is revealed after the baseline (T1) assessment is complete. This study protocol follows the Standard Protocol Items: Recommendations for Interventional Trials (SPIRIT) guidelines (see the SPIRIT checklist for this protocol in Additional file 1). Enrollment began in March 2018, and is recruiting at the time this report was prepared. We are running 3–4 cohorts of CBCT and 3–4 cohorts of the CHE group over 24 months, with 4–10 dyads in each cohort. HRQOL and healthcare adherence assessments as well as collection of biomarker samples are conducted before (T1), immediately after either 8-week intervention (T2), and then again 4–5 weeks later (T3). Overall study flow is depicted in Fig. 1. A study coordinator schedules assessment visits at the University of Arizona College of Nursing. Participants are also contacted the day before each assessment visit for a reminder, and to convey information about finding their way to the assessment site. If participants fail to complete study assessments at T2 (week 9), we attempt to collect data from them at T3 (week 13). Class attendance and at-home practice time (CBCT group only) are collected as measures of intervention engagement.

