**Fig. 1 Fig1:**
[figure not shown]
Diagram of study flow. CBCT® Cognitively-Based Compassion Training, CHE cancer health education

The randomization (allocation) sequence used to assign dyads to CBCT or CHE is generated using a computer program by someone not involved in other aspects of the study procedures (see acknowledgements below). Dyads are informed of their group assignment by a study coordinator. The coordinator who informs participants about their group assignment is not involved in recruitment, scheduling of study assessments, or administration of study assessments. The same coordinator only learns about a particular dyad’s group assignment from the individual who generates the allocation sequence after that dyad has completed T1 assessments. All other study personnel who are not interventionists remain blinded to group assignment throughout the study. Participants are asked to not discuss their group assignment with anyone other than a study coordinator who is not involved in administration of study assessments. In the event of an adverse event that is either related or unrelated to the trial unblinding will be permitted so that other members of the study team (i.e., the Principal Investigator or clinician co-Investigators) are able to respond appropriately. Participation in the study may be stopped if a participant is unable to complete a study assessment per protocol because of health status changes.

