### Power, data management plan, and analytic plan

As a preliminary effort, this study’s sample size was not determined based on power considerations. The goal is to estimate the effect sizes for the differences between the CBCT and CHE in the specified outcomes at weeks 9 and 13, so that the next definitive trial can be formally powered using the effect sizes estimated in this pilot study. Therefore, the sample size for this study (*n* = 40 dyads (80 participants total); CBCT *n* = 20, CHE attention control *n* = 20) is based on the number of cancer survivor-caregiver dyads projected to meet inclusion criteria and complete the entire study protocol in the study timeframe. The estimate of the effect size will be used to power the definitive trial, provided that the estimate falls into the range of clinically significant differences of 1/3 of the standard deviation or greater [62, 63]. The rigor of the proposed pilot randomized controlled trial design (i.e., having the CHE attention control) will secure the attribution of the effects to the intervention.

Questionnaire total scores, biomarker data, and other relevant endpoints (e.g., class attendance) will be entered into the study database and managed in SPSS (IBM Analytics, Armonk, NY, USA). Intervention fidelity will be summarized using the number of completed sessions.

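### A fixed block of two dyads makes the second arm of each pair certain once the first arm and the pairing are known, weakening concealment and staff blinding

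*Protocol article*

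**What the plan says.** The allocation rule in the protocol article is: "Enrolled dyads are randomized 1:1 in blocks of two dyads to either CBCT" or cancer health education (CHE), with 20 dyads planned per arm. No second block size, random variation of size or stratum is mentioned.

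The same section sets out the safeguards. The sequence is "generated using a computer program by someone not involved in other aspects of the study procedures". Release is late: "Group assignment to either CBCT or CHE is revealed after the baseline (T1) assessment is complete". The coordinator who tells dyads their arm "is not involved in recruitment, scheduling of study assessments, or administration of study assessments", and receives each assignment only once that dyad's baseline visit is done. For everyone else the section promises: "All other study personnel who are not interventionists remain blinded to group assignment throughout the study".

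It also describes ways in which an arm can become known. Participants know their arm and are asked not to discuss it, except with a coordinator who does not run assessments. Further, "In the event of an adverse event that is either related or unrelated to the trial unblinding will be permitted", so that the Principal Investigator or clinician co-investigators can respond. Consent is signed before either the Principal Investigator or a study coordinator. Under Study setting, blood draws, questionnaires and both arms' classes are all placed at the College of Nursing. Trial status says that recruitment was still open when the article was submitted.

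**The concern.** Blocking protects balance, but the smaller and more regular the block, the more one disclosed assignment says about the next. Two is the smallest possible block at 1:1, and the inference is then complete in both directions.

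Two things are at stake. The first is concealment: if someone with influence over entry knows that the next dyad will go to a given arm, the timing or encouragement of enrolment can be shaped by it, and adjustment for the baseline score does not reliably remove the resulting difference between arms. The second is the blinding of staff who schedule, assess and check questionnaires: one arm learned by chance can disclose a second. The section on power and analysis says that the effect sizes will feed the sample size of the definitive trial and relies on the controlled design for attribution, so bias at entry would carry forward.

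**Working it through.** **Inputs.** Block size 2, ratio 1:1, 40 dyads with 20 per arm (Study design; Power, data management plan, and analytic plan). No power formula applies, since "this study’s sample size was not determined based on power considerations". The documents give no leak rate; those below are assumptions.

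**The plan's own figure.** 40 / 2 = 20 blocks, each with one dyad per arm, gives 20 + 20. This matches the stated split.

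**Allocations that are certain.** In each block the second follows from the first: 20 × 1 = 20, and 20 / 40 = 50%.

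**Best guess by someone who knows all earlier allocations and the order.** First of each pair right half the time, second always: (20 × 0.5 + 20 × 1) / 40 = 30 / 40 = 75%, against 50% with no information.

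**Spread of a leak.** Suppose each dyad's arm becomes known to staff directly with probability q, independently, and staff know the pairing. Expected dyads with a known arm are 40q without pairing and 40 × [1 − (1 − q)²] with it.

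| Assumed q | Direct only | With blocks of two |
|---|---|---|
| 5% | 2.0 | 3.9 |
| 10% | 4.0 | 7.6 |
| 20% | 8.0 | 14.4 |
| 30% | 12.0 | 20.4 |

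At low rates the pairing nearly doubles the number exposed.

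**When selection is possible.** The first dyad's arm must be known before its partner enrols. Dyads enter 3–4 concurrent cohorts, and the interventions start about 2 weeks after screening. If each cohort closes before classes begin (an inference; the article does not say so), leaks from classes or from adverse events during the intervention come after most partners are enrolled. The exceptions are a block left open across a cohort boundary (2–3 boundaries, so at most 2–3 dyads) and the interval between a dyad being told its arm and its partner enrolling.

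**Alternatives, in the same worst case of full knowledge of earlier allocations.** Fixed blocks are by exact enumeration. Mixtures are simulated (4,000 sequences of 40), with a guesser who knows the possible sizes but not the size of each block.

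| Scheme | Certain | Best guess right |
|---|---|---|
| Fixed 2 (as planned) | 50% | 75% |
| Fixed 4 | 33.3% | 70.8% |
| Random 2/4 | 10.8% | 72.0% |
| Random 4/6 | 5.6% | 68.9% |
| Random 2/4/6 | 4.1% | 69.9% |

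**Whole-cohort randomisation.** Every dyad is enrolled and assessed at baseline before any arm in that cohort exists, so there is no within-cohort foreknowledge at entry. For a cohort of 2k dyads, knowing one arm puts any other dyad in the opposite arm with probability k / (2k − 1). Reading the stated 4–10 dyads as per class, this is 4/7 = 57% to 10/19 = 53%, against 100% with pairs.

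**The case against.** The strongest reply is that the firewalls are real and that exploiting the pairs takes two pieces of knowledge: one dyad's arm, and which dyad is its partner. The sequence sits with an independent person, arms are released one dyad at a time after baseline, and the messenger has no part in recruitment. Nothing says that recruiters or assessors were told the block size, and the full protocol is not shown. This stands, and it makes the 50% a ceiling and not an expected rate.

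A reader might infer that any adverse event unblinds the Principal Investigator, and that this person enrols the dyads. The text supports neither: unblinding is permitted, not automatic, and consent may be taken by a coordinator instead. A reader might also infer that each unblinding necessarily exposes two dyads. It does so only for someone who can identify the pair.

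Three further points limit the consequence:

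- Many leaks would come after the partner is enrolled, when they can affect staff blinding but not selection.
- The primary outcome is self-reported by participants who know their arm, so lost staff blinding bears more on visit handling and completeness checks than on scoring.
- The article appeared on 29 April 2019 and expects all procedures to end by September 2019. With the last assessment at week 13, the final classes would start around June 2019, so few allocations may have remained. The 24 months given under Study design would allow more.

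Finally, varying block sizes nearly eliminate certain allocations but improve guessing only modestly, from 75% to about 70%, roughly 2 of 40 allocations. That also stands, and is a reason to prefer whole-cohort randomisation.

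None of this removes the weakness. The safeguards rest partly on a request to participants in class-based arms that share a site with the assessments, and the smallest possible block gives no margin if an arm does slip out.

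**Conclusion.** The point holds in limited form. The fixed block of two is a stated choice that makes the second member of a pair certain once the first member's arm and the pairing are known. The documents do not show that concealment has failed or that half the arms were predictable in practice. They show a design in which a leak, if it occurs, carries further than it need.

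The size is at most 20 of 40 allocations determined, with a best-guess rate of at most 75%. Selection bias is plausible mainly for the few dyads not yet enrolled when their partner's arm becomes known. For the rest, the effect is that one leak can cost staff blinding for two dyads (4 participants). This rests on the block size being known or guessed, on the enrolment order being visible to staff, and on an unknown leak rate. For an unpowered pilot the weakness is moderate, but it is avoidable and should be changed if allocations remain.

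**What to change.** **Preferred, for allocations not yet issued.** The independent generator randomises all dyads of a starting cohort together, balanced 1:1, once the whole cohort has completed its baseline assessments. Classes already start in concurrent cohorts, so this fits the schedule and keeps the two classes of equal size (within one dyad if the cohort is odd).

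**Alternative.** Randomly varying block sizes, for example 2, 4 and 6, with the sizes withheld from site staff. The price is slightly unequal classes, which matters more when a class may hold as few as 4 dyads.

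**Cost.** A new list for the remaining dyads and a short amendment. Under the preferred option, dyads learn their arm slightly later.

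**If no allocations remain.** Report the fixed block of two as a limitation alongside the effect sizes, and do not use it in the definitive trial.
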